### Follow-Up

During the 24-month study period, data will be collected at the following post-treatment/procedure timepoints: 3 days, 1, 3, 6, 12, and 24 months (Table 2). A standardized electronic case report form will be used to collect clinical data across all participating centers. As available, collected data will include demographics, medical history, physical assessments, medications, magnetic resonance imaging, quality-of-life questionnaires (e.g., 12-Item Short Form Health Survey, WOMAC), pain assessment via completion of the NRS, and adverse events. Data will be entered into the secure, web-based, electronic case report form. The inputted data will be reviewed by a combination of automatic programmed queries and manual review to identify inconsistent and missing data entries for resolution.

**Table 2 Tab2:** Data collection schedule

Data	Baseline^a,b^	Day 0 Index procedure	3 days (3 ± 2 days) (Phone)	1 month (30 ± 7 days)	3 months (90 days ± 10 days)	6 months (180 ± 15 days)	12 months (360 ± 30 days)	24 months (720 ± 60 days)
Informed consent^c^	X							
Inclusion/exclusion criteria evaluation	X	X				X^d^		
Demographics	X							
Medical history	X							
Physical examination	X			X	X	X	X	X
Pregnancy test (if applicable per standard of care)^b^	X					X^d^		
Medications (NSAIDs/corticosteroids/ analgesics)	X	X		X	X	X	X	X
MRI	X^e^					X^e,f^	X^f^	
WOMAC	X			X	X	X	X	X
SF-12	X			X	X	X	X	X
Numerical Rating Scale	X			X	X	X	X	X
Adverse events^g^	X^g^	X	X	X	X	X	X	X

MRI, magnetic resonance imaging; NSAIDs, non-steroidal anti-inflammatory drugs; SF-12, 12-Item Short Form Health Survey; WOMAC, The Western Ontario and McMaster Universities Arthritis Index

^a^Standard of care assessments may be done up to 30 days before the procedure. Protocol-specific assessments/examinations that are non-standard of care cannot be obtained until after informed consent is obtained

^b^Pregnancy test (sites should follow their institutional policy/standard of care for pregnancy testing in females of child-bearing age prior to angiography)

^c^Informed consent to be obtained within 30 days prior to enrollment

^d^Crossover patients only

^e^Baseline MRI required of both groups—may be obtained up to 180 days prior to randomization/enrollment; 6-month follow-up MRI required of treatment group only (GAE group)

^f^MRI at 6-month visit and 12-month visit only required for patients that crossover to GAE treatment (not applicable to GAE to steroid injection crossover)

^g^Adverse events to be collected beginning at time of treatment following randomization

Any patient who receives a partial or total knee replacement of the targeted knee, or who is non-compliant will be withdrawn. Investigators may also withdraw any patient from the study that is deemed to be in the best interest of the patient. Patients will be encouraged to complete a final study exit visit at the time of withdrawal to assess for safety. Any data collected up to the time the patient is withdrawn from the study will be maintained as part of the study record and analyzed as appropriate.

If a patient discontinues the study at any time, is withdrawn from the study early, or completes all protocol required follow-up, they will be followed per the local standard of care for their condition.

Any patient who withdraws from the trial, or is lost to follow-up, will not be replaced.

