### Eligibility Criteria

Table 1 summarizes the full list of eligibility criteria. Patients with confirmed knee osteoarthritis who meet all of the general inclusion criteria and none of the general exclusion criteria will be randomized into one of two arms: the treatment arm (i.e., GAE) or the control arm (i.e., corticosteroid injection). Patients who are assigned to the treatment arm are screened to ensure that they meet all angiographic eligibility criteria (Table 1) before they can undergo GAE. Patients randomized to the treatment arm who do not meet the angiographic eligibility criteria are considered an angiographic screen failure and will be followed through discharge only. Any patient who is randomized into the study, but later found to have not met all eligibility criteria will remain in the study and complete all trial testing and follow-up requirements.

**Table 1 Tab1:** Key inclusion and exclusion criteria

*General inclusion criteria*
Provides written informed consent Age ≥ 21 years Mild to severe knee pain, defined as a WOMAC Pain score of ≥ 8 out of 20 (in the target knee) Pain refractory to conservative therapies (e.g., anti-inflammatory drugs, or physical therapy, or muscle strengthening, or intra-articular injections) for at least 90 days prior to enrollment/randomization Kellgren–Lawrence grade 1, 2, 3, or 4 on radiograph of the knee within 6 months of enrollment/randomization (of the target knee)
*General exclusion criteria*
Planned major surgical or endovascular procedures ≤ 30 days after the index procedure Advanced atherosclerosis Known history of rheumatoid or infectious arthritis Received corticosteroid injection(s) in the target knee ≤ 90 days prior to treatment following enrollment/randomization Prior knee replacement surgery of the target knee
*Angiographic inclusion criteria*
Patient has confirmed evidence of knee osteoarthritis, defined as an angiographic ‘blush’ pattern (radiographic) in one or more of the target genicular artery(ies) Patient requires ≤ 4 genicular arteries to be treated
*Angiographic exclusion criteria*
Patient has evidence of arterial occlusion precluding catheterization (e.g., inability to cross iliac or superficial femoral artery(ies) and gain access to the genicular arteries) Patient has total occlusion of the genicular arteries on the target knee

WOMAC, The Western Ontario and McMaster Universities Arthritis Index

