#### Enrollment and Randomization

The MOTION study will enroll 264 patients across up to 45 centers, with a maximum of 15 centers allowed to be outside of the USA. Enrollment will not exceed 20% of total study population at any one center.

Patients will be randomized (1:1) to GAE or corticosteroid injection following confirmation that all eligibility criteria are met (Table 1).

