#### Intervention

##### Treatment Arm

For patients randomized to the treatment arm (GAE), a baseline angiogram will be obtained to determine final eligibility prior to inserting the embolic agent into the vasculature.

An intra-arterial sheath will be placed via femoral access (ipsilateral or contralateral) for the GAE procedure. Radial and pedal access are not permitted in this trial. Prior to treatment with the embolic agent (Embosphere® Microspheres, 100–300 µm; Merit Medical Systems, Inc.), angiography will be performed according to standard of care at each participating center and in accordance with requirements from the core laboratory, to confirm the presence of hyperemia (i.e., ‘blush’ pattern, Fig. 1) within the synovial tissues surrounding the affected knee joint in accordance with the angiographic criteria (Table 1). If confirmed, the genicular artery(ies) will be assessed to identify culprit vessels contributing to the hypervascularity of the synovial tissue in the region of the knee joint.

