### Statistical Analysis

The proportion of the patients in the treatment and control arms achieving clinical success at 6 months will be compared. The hypothesis that treatment (GAE) is superior to control (corticosteroid injection). The number of patients needed to assess clinical success at 6 months was determined using a two-group Chi-square test based on the following assumptions: a clinical success rate of 65% for the treatment arm [12, 16] and a 40% clinical success rate for the control arm [8, 20, 21].

For the safety endpoint, treatment is hypothesized to be noninferior to control. The number of patients needed to assess the primary safety outcome was based on the following assumptions: (1) event-free safety rate of 95% in the treatment arm [11–14, 16, 22–24]; (2) event-free safety rate of 95% in the control arm [8]; (3) non-inferiority margin of 10%; (4) one-sided alpha of 0.025; (5) 85% statistical power; and (6) 15% attrition rate.

A required sample size of 264 patients (132 per arm) inclusive of a 15% attrition was determined. The overall study power is > 80%.

For purposes of endpoint determinations, the intent-to-treat (ITT) analysis set will include all randomized patients in both arms, and the modified ITT (mITT) analysis set will include all ITT patients who receive treatment and exclude patients that failed angiographic screening. The mITT analysis set will be used to evaluate the primary efficacy and safety outcome measures.

Continuous study measures will be summarized using descriptive statistics (mean, standard deviation, median, minimum, and maximum). Categorical or binary outcomes will be summarized using percentage with confidence intervals as appropriate.

Kaplan–Meier plots will be used to summarize time-to-event data. Continuous variables will be evaluated with independent t-tests. The threshold for statistical significance is *p* < 0.05.

Outcomes of crossover patients will be reported on a mITT basis and analyzed as separate populations (CtT and CtC).

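### GAE-arm patients who fail angiographic screening after arterial access are left out of the primary safety test and followed only to discharge, so any harm to them never enters the comparison

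*Protocol article*

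**What the plan says.** All references are to the protocol article.

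- **Order of events.** Enrollment and Randomization: "Patients will be randomized (1:1) to GAE or corticosteroid injection following confirmation that all eligibility criteria are met". Eligibility Criteria then adds a second screen for one arm only: "Patients who are assigned to the treatment arm are screened to ensure that they meet all angiographic eligibility criteria".
- **What that screen involves.** Treatment Arm: "a baseline angiogram will be obtained to determine final eligibility prior to inserting the embolic agent into the vasculature", and "An intra-arterial sheath will be placed via femoral access (ipsilateral or contralateral) for the GAE procedure".
- **What happens to failures.** Eligibility Criteria: they "are considered an angiographic screen failure and will be followed through discharge only". The next sentence of that section gives a general rule pointing the other way: a randomised patient later found ineligible stays in the trial and completes every test and visit.
- **Safety analysis set.** Statistical Analysis defines mITT as ITT patients who were treated, without those who failed angiographic screening, and then states: "The mITT analysis set will be used to evaluate the primary efficacy and safety outcome measures".
- **Safety endpoint.** Primary Outcome Measures: freedom from treatment-related safety events through 180 days after the index procedure. Statistical Analysis tests it for non-inferiority with a 10% margin.
- **Start of adverse-event collection.** Table 2, footnote g: "Adverse events to be collected beginning at time of treatment following randomization".

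**The concern.** A screen failure in the GAE arm has been exposed to an invasive, protocol-directed procedure because of the randomised assignment. The plan removes that patient from the primary safety denominator and ends observation at discharge. An access or angiography complication seen before discharge does not count in the test, and one that appears later has no planned route into the data.

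The exclusion is made after randomisation and can occur in one arm only. The mITT condition of having received treatment applies to both arms, but controls have no angiographic screen to fail. The trial's safety claim is that GAE is not inferior to injection, and a patient choosing GAE accepts the angiogram as part of it. Leaving out failures may be defensible for efficacy. For safety, exposure to the procedure is the natural basis for the set.

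A later ITT safety analysis could not repair this, because post-discharge events in these patients would not have been collected.

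**Working it through.** **1. Reproduce the planned sample size.** Inputs from Statistical Analysis: 95% event-free in each arm, margin 10 points, one-sided alpha 0.025, power 85%, attrition 15%.

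- The Farrington-Manning score formula uses null-restricted rates of 0.9703 (control) and 0.8703 (GAE). Null variance term: 0.8703 × 0.1297 + 0.9703 × 0.0297 = 0.1417. Alternative variance term: 2 × 0.95 × 0.05 = 0.095.
- n per arm = [(1.960 × √0.1417 + 1.036 × √0.095) / 0.10]² = 111.7, so 112.
- 112 / 0.85 = 131.8, so 132 per arm and 264 in total, matching the plan.
- Power at 112 per arm is 0.851 for safety and 0.967 for efficacy (65% vs 40%). The product, 0.823, agrees with the stated overall power above 80%.

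The sample size is not in error. (The unpooled Wald formula gives 86 per arm, or 102 after attrition, and does not reproduce the plan.)

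**2. Follow one screen failure through the rules.**

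| Step | GAE-arm screen failure | Control |
|---|---|---|
| Invasive step after randomisation | Femoral sheath and angiogram | Injection |
| Can fail a screen during the procedure | Yes | No |
| Planned follow-up | To discharge (specific rule) | To 24 months |
| In primary safety set | No | Yes, if treated |

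Events in failures add zero to the GAE count in the safety test, whatever their true rate.

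**3. Effect on the tested rate.** Let f be the share of GAE-arm patients who fail screening and e their event rate. The document gives neither, so both are assumed. Treated GAE patients and controls are held at the planned 95%.

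GAE event-free rate with failures included = (1 − f) × 95% + f × (100% − e) = 95% + f × (5% − e).

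| f | e = 0 | e = 5% | e = 10% | e = 20% |
|---|---|---|---|---|
| 2% | 95.1% | 95.0% | 94.9% | 94.7% |
| 5% | 95.25% | 95.0% | 94.75% | 94.25% |
| 10% | 95.5% | 95.0% | 94.5% | 93.5% |

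The shift runs from +0.5 to −1.5 points. At f = 20% the same formula gives 0.20 × 5 = +1.0 to 0.20 × (5 − 20) = −3.0 points.

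**4. Effect on safety power** (Farrington-Manning, 112 controls; GAE arm 112 with failures included, 112 × (1 − f) with them excluded, so failures are assumed to come on top of the 15% attrition).

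| f | Excluded | Included, e = 0 | Included, e = 5% | Included, e = 20% |
|---|---|---|---|---|
| 2% | 0.844 | 0.860 | 0.851 | 0.821 |
| 5% | 0.834 | 0.874 | 0.851 | 0.771 |
| 10% | 0.815 | 0.895 | 0.851 | 0.678 |

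Inclusion can raise or lower power, depending on e.

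**The case against.** **Direction.** A reader might infer that the exclusion can only favour GAE. For the event count that is so: exposed patients are removed and nothing is added. The test, however, compares proportions. Failures receive no embolic agent and avoid the non-target embolization risk that the Treatment Arm section names, so their event rate may well be below 5%. In that case including them raises the GAE event-free rate, and leaving them out works against the sponsor. This objection stands; the documents do not support calling the exclusion anti-conservative.

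**Size.** A reader might also assume a 5% event rate among failures and conclude that the GAE rate would drop by a point. It would not: mixing patients at 5% with patients at 5% leaves 95%. A one-point fall needs, for example, f = 20% with e = 10%, or f = 10% with e = 15%.

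**Footnote g.** Time of treatment can be read to include the angiogram, since the sheath is described as part of the GAE procedure and Table 2 collects adverse events on the index-procedure day. This also stands. The footnote is ambiguous and only supporting; the point rests on the discharge-only rule and the mITT definition.

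**Observation.** It would be too strong to say that these patients go unobserved. They are followed to discharge, when acute events can be seen, and the general rule in Eligibility Criteria would keep them in full follow-up. The discharge-only rule is the more specific of the two, so it is the likelier to be applied, but the text conflicts.

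None of this answers the core point. Even events seen before discharge stay outside the primary safety test.

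**Conclusion.** The point holds as a defect in the safety set and in safety follow-up. As written, patients exposed to arterial access and angiography in one arm, and any harm to them, are kept out of the primary safety comparison, and their harms after discharge are not systematically collected.

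The effect on the result cannot be sized from the document. Against a 10-point margin, the GAE event-free rate would move by about +0.5 to −1.5 points under the assumed f of 2–10% and e of 0–20%, and not at all at e = 5%. These figures also assume that treated GAE patients and controls run at the planned 95%. The case for change does not depend on the size: it rests on who was exposed and whether their harms are recorded.

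**What to change.** 1. In Eligibility Criteria, reconcile the discharge-only rule for angiographic screen failures with the rule that randomised patients later found ineligible complete all follow-up.
2. In Table 2, footnote g, state that adverse-event collection starts at arterial access or needle insertion, whether or not treatment follows.
3. Collect safety data from screen failures at the contacts already in Table 2, with event status through 180 days.
4. In Statistical Analysis, analyse the safety endpoint in all randomised patients in whom the index procedure was started, at least alongside the mITT result, and show screen failures separately. The separate display keeps the event rate of embolization itself visible. Say also that an angiogram without embolization counts as a started index procedure, since the Abstract describes the index procedure only as GAE or injection.

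**Cost.** Wording changes, plus a few contacts each for about 7 to 26 patients (132 × 0.05 = 6.6; 132 × 0.20 = 26.4, on an assumed failure share of 5–20%). The GAE event-free rate may move slightly either way. No change to the sample size is needed unless the planning rates are revised. The data-collection changes should come early, because later events in patients already discharged are not being gathered.

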## Data Monitoring

Throughout the study, the sponsor will conduct monitoring visits using a risk-based approach to verify that the study is being conducted in accordance with the protocol and good clinical practice, and to verify that critical data points, endpoint and safety data are accurately and completely documented in accordance with source medical records. The study will be audited in accordance with the sponsor’s audit program, including audit of investigational sites.

Safety events will be classified according to the International Organization for Standardization (ISO 14155:2020) definitions. An independent Clinical Events Committee (Yale Cardiovascular Research Group), of at least three independent physicians with experience performing GAE, will be responsible for systematic review and adjudication of specified safety events.

### Statistical Analysis

The proportion of the patients in the treatment and control arms achieving clinical success at 6 months will be compared. The hypothesis that treatment (GAE) is superior to control (corticosteroid injection). The number of patients needed to assess clinical success at 6 months was determined using a two-group Chi-square test based on the following assumptions: a clinical success rate of 65% for the treatment arm [12, 16] and a 40% clinical success rate for the control arm [8, 20, 21].

For the safety endpoint, treatment is hypothesized to be noninferior to control. The number of patients needed to assess the primary safety outcome was based on the following assumptions: (1) event-free safety rate of 95% in the treatment arm [11–14, 16, 22–24]; (2) event-free safety rate of 95% in the control arm [8]; (3) non-inferiority margin of 10%; (4) one-sided alpha of 0.025; (5) 85% statistical power; and (6) 15% attrition rate.

A required sample size of 264 patients (132 per arm) inclusive of a 15% attrition was determined. The overall study power is > 80%.

For purposes of endpoint determinations, the intent-to-treat (ITT) analysis set will include all randomized patients in both arms, and the modified ITT (mITT) analysis set will include all ITT patients who receive treatment and exclude patients that failed angiographic screening. The mITT analysis set will be used to evaluate the primary efficacy and safety outcome measures.

Continuous study measures will be summarized using descriptive statistics (mean, standard deviation, median, minimum, and maximum). Categorical or binary outcomes will be summarized using percentage with confidence intervals as appropriate.

Kaplan–Meier plots will be used to summarize time-to-event data. Continuous variables will be evaluated with independent t-tests. The threshold for statistical significance is *p* < 0.05.

Outcomes of crossover patients will be reported on a mITT basis and analyzed as separate populations (CtT and CtC).

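### The primary analysis set drops angiographic screen failures, who can arise only in the GAE arm and only after randomisation, and their 6-month outcomes are not collected

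*Protocol article*

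**What the plan says.** The design is fixed in four places in the protocol article.

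- **Who has the angiogram.** Eligibility Criteria: "Patients who are assigned to the treatment arm are screened to ensure that they meet all angiographic eligibility criteria". The Treatment Arm section places it after allocation: "a baseline angiogram will be obtained to determine final eligibility prior to inserting the embolic agent into the vasculature". No angiogram is described for controls at entry.
- **What follows a failure.** Eligibility Criteria says that GAE patients who do not meet the angiographic criteria "are considered an angiographic screen failure and will be followed through discharge only".
- **The analysis sets.** Statistical Analysis defines ITT, in that "the intent-to-treat (ITT) analysis set will include all randomized patients in both arms", and then mITT, in that "the modified ITT (mITT) analysis set will include all ITT patients who receive treatment and exclude patients that failed angiographic screening".
- **Which set is primary.** "The mITT analysis set will be used to evaluate the primary efficacy and safety outcome measures".

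Table 1 lists the angiographic criteria. They require a blush pattern in at least one target artery and no more than four arteries to treat, and they rule out certain arterial occlusions.

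**The concern.** Randomisation makes the two arms comparable as allocated. The mITT rule then removes GAE patients on the basis of a finding made after allocation, by an examination that controls do not have. Controls with no blush, with occluded vessels or with too many arteries to treat cannot be recognised, so they stay in.

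The article's Introduction ties synovial hypervascularity to inflammation and pain, and Table 1 treats blush as evidence of the disease. On that rationale, blush could plausibly relate to the response to a steroid as well as to GAE. If it does, the primary contrast mixes a treatment effect with a selection effect.

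The usual safeguard is an ITT analysis. Here it is weakened because the excluded patients have no 6-month WOMAC.

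The primary safety outcome is also affected. Screen failures undergo arterial access and angiography as part of their allocated arm, yet they are outside the primary safety set and unobserved after discharge. The endpoint runs to 6 months.

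**Working it through.** **1. The plan's own figure.** The inputs, from Statistical Analysis, are 95% event-free in each arm, a 10-point margin, one-sided alpha 0.025, 85% power and 15% attrition. The Farrington-Manning score formula has restricted null rates of 0.870 and 0.970.

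n = (1.96√0.1417 + 1.036√0.095)² / 0.10² = 111.7, so 112 per arm. Then 112/0.85 = 131.8, so 132 per arm and 264 in total.

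The stated size reproduces exactly. At 112 per arm, power for 65% versus 40% is 96.7% and safety power is 85.1%. Their product is 82.3%, in line with the stated figure above 80%. The problem lies in the analysis set and the follow-up, not in this arithmetic.

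**2. Error of the mITT superiority test.** Assumptions, because the article gives no figures:
- f is the share of patients who fail, or in the control arm would have failed, the angiogram: 5-20%, or 132 × 0.05 = 7 to 132 × 0.20 = 26 GAE patients.
- s is the success rate on steroid of controls who would have failed: 20-50%.
- GAE is no better than steroid in eligible patients, with success of 40% on both.
- The test is two-sided at 0.05, so 2.5% in the direction favouring GAE.

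Formulas:
- GAE rate in mITT: pT = 0.40, with nT = 132 × 0.85 × (1−f)
- Control rate in mITT: pC = 0.40(1−f) + s·f, with nC = 112
- Error = Φ[(pT − pC − 1.96·SE₀)/SE₁], where SE₀ is the pooled and SE₁ the unpooled standard error

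Example, f = 10% and s = 20%: pC = 0.38, nT = 101.0 and SE₀ ≈ SE₁ ≈ 0.0669. Then (0.02 − 0.1312)/0.0669 = −1.66, which gives 4.8%.

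| s | f = 5% | 10% | 15% | 20% |
|---|---|---|---|---|
| 20% | 3.5% | 4.8% | 6.5% | 8.4% |
| 30% | 3.0% | 3.5% | 4.1% | 4.8% |
| 40% | 2.5% | 2.5% | 2.5% | 2.5% |
| 50% | 2.1% | 1.7% | 1.5% | 1.2% |

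**3. What ITT could say without the missing outcomes.** If 65% of the retained GAE patients succeed, the all-randomised GAE rate lies between 0.65(1−f) and 0.65(1−f) + f. That is 61.8-66.8% at f = 5%, 58.5-68.5% at 10% and 52.0-72.0% at 20%.

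**4. Efficacy power of an ITT test at 112 per arm** (96.7% with no screen failures):
- *Screen failures and their control counterparts both succeed at 20%.* At f = 10%, GAE is 0.9 × 65 + 0.1 × 20 = 60.5% and control is 0.9 × 40 + 0.1 × 20 = 38.0%, giving 92.6% power. At f = 15%, 58.3% versus 37.0% gives 89.5%.
- *GAE screen failures counted as non-success, control at 40%.* At f = 10%, 58.5% versus 40% gives 79.5%. At f = 15%, 55.3% versus 40% gives 62.9%.

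**The case against.** **An ITT set is defined, and its use and imputation rules belong in the analysis plan.** This stands in part. The analysis plan is not shown, and an ITT result can still be produced by counting screen failures as non-success or by bounding. A reader might infer that ITT cannot be computed at all; the article does not support that. However, the choice of primary set and the discharge-only rule are both fixed here, and no analysis plan can recover 6-month data that were never collected.

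**mITT answers the question for patients who can be embolised.** That is a legitimate question, but it needs a control group of patients who could be embolised, and none is identified.

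**Bias is not shown.** This stands. A reader might infer that the design inflates the apparent benefit of GAE. The documents give neither the share nor the prognosis of screen failures. The error stays at 2.5% if would-be failures do as well as other controls, and falls below it if they do better.

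**The exclusion is not wholly one-sided.** mITT also requires receipt of treatment, and that applies in both arms. The angiographic exclusion can occur only in the GAE arm.

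**The eligibility text is not truly contradictory.** A reader might see a conflict between discharge-only follow-up and the rule that patients "randomized into the study, but later found to have not met all eligibility criteria will remain in the study". The ordinary reading is a specific rule followed by a general one. Likewise, Enrollment and Randomization places randomisation "following confirmation that all eligibility criteria are met (Table 1" although Table 1 includes the angiographic criteria. Eligibility Criteria and Treatment Arm make the order clear. Both are points of wording.

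**Conclusion.** The concern holds as a risk of bias of unknown size and direction in both primary comparisons. It rests on stated text: an angiogram in one arm after randomisation, exclusion of those who fail it from the primary set, and no follow-up of them past discharge.

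For screen-failure shares of 5-20%, the one-sided error of the superiority test could lie anywhere from about 1.2% to 8.4% against a nominal 2.5%, as the prognosis of would-be failures on steroid moves from 50% to 20% success. These ranges depend on the assumed share, prognosis and null. They show what the design permits; they do not estimate what will happen.

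For safety, no size can be given, because the article has no event rate for patients who have angiography without embolisation. The gap in observation is nonetheless plain. The sample size of 264 is not in question.

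**What to change.** 1. In Eligibility Criteria, replace discharge-only follow-up of angiographic screen failures with collection of WOMAC, NRS, additional interventions and adverse events through at least 6 months, on the Table 2 schedule.
2. In Statistical Analysis, analyse ITT with a prespecified rule for how screen failures count. Preferably make it the primary superiority test with mITT supportive. If mITT must stay primary, report ITT beside it and claim superiority only if both agree.
3. Report the safety outcome for all randomised patients as well as for mITT.
4. Wording only: say how the screen-failure rule and the general rule for ineligible patients fit together, and refer to the general criteria, not all criteria, in Enrollment and Randomization.

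The cost is questionnaire and adverse-event follow-up of perhaps 7-26 patients, plus some power. With 10% or 15% screen failures, efficacy power at 112 per arm falls from about 97% to 92.6% or 89.5% if these patients succeed at 20% in both arms. It falls to 79.5% or 62.9% if GAE screen failures count as non-success against 40% in controls. The rule chosen therefore matters and should be set in advance. The change is best made early, because the 6-month outcome of each screen failure not followed is lost.

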### Primary Outcome Measures

The primary efficacy outcome measure is the proportion of patients achieving clinical success at 6 months (180 days), defined as ≥ 50% improvement in the Western Ontario and McMaster Universities Osteoarthritis Index (WOMAC) Pain Subscale from baseline without the need for additional intervention (i.e., rescue treatment for inadequate pain relief such as intra-articular steroid injection or other interventions, exclusive of vascular intervention such as GAE).

The primary safety outcome is the freedom from treatment-related safety events through 6 months (180 days) following the index procedure.

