### Additional Outcome Measures

Secondary outcome measures will include: the number of patients who achieve clinical success at 3, 12, and 24 months; patient rating of pain at baseline, 3, 6, 12, and 24 months as assessed using the Numerical Rating Scale (NRS); the number of patients who achieve ≥ 50% reduction in the mean NRS pain score at 3, 6, 12, and 24 months. Additional secondary outcome measures will include assessments of technical success (defined as successful procedural occlusion of the target genicular arteries confirmed fluoroscopically by the treating physician), device-related and serious adverse device effects through 24 months, in addition to symptom-related changes throughout the study period. Exploratory endpoints will include, as available, the number of patients that progress to partial or total knee replacement and outcomes in any crossover patients will also be described.

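### Independent t-tests for continuous outcomes are valid but give up precision that the scheduled baseline scores would supply

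*Protocol article*

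**What the plan says.** Protocol article, Statistical Analysis: "Continuous variables will be evaluated with independent t-tests", with significance declared at p < 0.05. The section names no covariate, ANCOVA or repeated-measures model. It does not say whether the quantity tested is the follow-up score or the change from baseline.

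Protocol article, Follow-Up: the data collected include "quality-of-life questionnaires (e.g., 12-Item Short Form Health Survey, WOMAC), pain assessment via completion of the NRS". Table 2 marks WOMAC, SF-12 and NRS at baseline and at 1, 3, 6, 12 and 24 months, for both arms. WOMAC Pain is also an entry criterion (at least 8 of 20), so it should be known for every eligible patient.

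Protocol article, Additional Outcome Measures: the NRS pain rating at baseline, 3, 6, 12 and 24 months is a named secondary outcome.

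Protocol article, Primary Outcome Measures: "The primary efficacy outcome measure is the proportion of patients achieving clinical success at 6 months (180 days"). The primary safety outcome is likewise the proportion free of events. The t-test sentence therefore governs secondary continuous measures only.

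Protocol article, Study Cohorts: patients without clinical success may cross over, in either direction, once the 6-month visit is complete.

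**The concern.** The article commits to a specific method that makes poorer use of the data than a standard alternative. A patient's pain score at follow-up is usually correlated with the same patient's score at entry. A two-sample t-test cannot take the right account of that correlation. On follow-up scores it gives baseline a weight of zero; on change scores it gives baseline a weight of one. Regression lets the data set the weight, which normally lies between the two.

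Two things are at stake for the secondary continuous outcomes. Confidence intervals for the treatment difference are wider than they need to be. In addition, if the arms happen to differ at baseline, the estimate carries part of that difference: in one direction for follow-up scores, in the other for change scores.

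**Working it through.** **1. The plan's own figure.** The 264 is reproduced by the safety non-inferiority calculation: 95% event-free in both arms, margin 10 points, one-sided alpha 0.025, power 85%. The Farrington-Manning score method has restricted null rates of 0.870 and 0.970. It gives n = [1.96 × √(0.870×0.130 + 0.970×0.030) + 1.036 × √(2×0.95×0.05)]² / 0.10² = 111.7 when unrounded rates are used, so 112 per arm. Then 112/0.85 = 131.8, so 132 per arm and 264 in total. No t-test enters this, so the sample size does not depend on the point made here. The 112 evaluable per arm is used below.

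**2. Inputs that the documents do not give.** They state neither the standard deviation of any scale nor the baseline to follow-up correlation ρ. Results are therefore in SD units, for assumed ρ of 0.3, 0.5 and 0.7, with equal SD at baseline and follow-up.

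**3. Variance of the treatment difference under ANCOVA.**
- Relative to a t-test on follow-up scores: 1 − ρ².
- Relative to a t-test on change scores: (1 − ρ²)/[2(1 − ρ)] = (1 + ρ)/2.

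| ρ | vs follow-up scores | reduction | vs change scores | reduction |
|---|---|---|---|---|
| 0.3 | 0.91 | 9% | 0.65 | 35% |
| 0.5 | 0.75 | 25% | 0.75 | 25% |
| 0.7 | 0.51 | 49% | 0.85 | 15% |

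Precision is lost whichever score the t-test uses. At ρ = 0.5 the t-test needs 1/0.75 − 1 = 33% more patients for the same precision.

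**4. In terms of power.** With 112 per arm the standard error of a mean difference is √(2/112) = 0.134 SD, and a follow-up-score t-test has 80% power for 2.80 × 0.134 = 0.374 SD. ANCOVA power for the same effect is Φ(2.80/√(1 − ρ²) − 1.96): 83.6%, 89.9% and 97.5% at ρ = 0.3, 0.5 and 0.7. Where a change-score t-test has 80% power, ANCOVA has Φ(2.80/√((1 + ρ)/2) − 1.96): 93.5%, 89.9% and 86.0%.

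**5. Chance baseline imbalance.** Take a baseline difference of 1.96 standard errors, 1.96 × 0.134 = 0.26 SD. A follow-up-score comparison is shifted by ρ × 0.26 = 0.08, 0.13 or 0.18 SD. A change-score comparison is shifted the other way by (1 − ρ) × 0.26 = 0.18, 0.13 or 0.08 SD. Given an imbalance of exactly that size, the type I error of the follow-up-score test is 1 − Φ[1.96(1 − ρ)/√(1 − ρ²)] + Φ[−1.96(1 + ρ)/√(1 − ρ²)], that is 7.9%, 12.9% or 20.5%. Averaged over all randomisations it remains 5%.

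**The case against.** The strongest reply is that this is an efficiency preference and not an error. Under randomisation a two-sample t-test is unbiased, and its standard error already allows for chance imbalance. The 7.9% to 20.5% figures apply only when a notable imbalance has occurred. No primary conclusion depends on the test. The gain rests on an assumed ρ and can be modest: at ρ = 0.3, power against the follow-up-score test rises only from 80% to 83.6%. The WOMAC entry threshold truncates the baseline range and may lower ρ for that scale. All of this stands.

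It can also be said that covariates are commonly left to the analysis plan, which is not shown. That has less force, because the article does not stay silent: it names a test. If the analysis plan already contains an adjusted model, the article's sentence misdescribes it and the two should be aligned.

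Some stronger readings are tempting but go beyond the text. A reader might infer that the test is run separately at each visit on observed cases only, so that the planned 15% attrition removes patients who have earlier data. The article says none of this; its 15% is a sample-size allowance, not a rule for missing scores. A reader might also infer that baseline is ignored altogether. That holds only if follow-up scores are tested; with change scores it is used, but with too much weight. Finally, SF-12 is collected but not named in either outcome section, so the argument should rest mainly on the NRS rating.

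**Conclusion.** The point holds as one of efficiency. The article fixes a valid but inefficient test for its secondary continuous outcomes although the baseline value of each scale is scheduled for everyone. The variance penalty is avoidable under either reading of the t-test. Its size depends on ρ, which is assumed, and on equal SDs at the two times. The primary endpoints, the 264 patients and the stated power do not change.

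The finding should not be read as a claim that the t-test inflates the overall type I error. Nor does baseline adjustment repair the exclusion, after randomisation and in the GAE arm only, of patients who fail angiographic screening; that is a separate matter. The change is worth making, but no main conclusion of the trial turns on it.

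**What to change.** Replace the t-test sentence with a baseline-adjusted analysis, in the protocol and the analysis plan, before outcome data are examined by arm:

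- Use ANCOVA at each visit, or one mixed model for repeated measures with arm, visit and arm-by-visit, in each case with the baseline value of the same scale as covariate.
- Report adjusted mean differences with 95% CIs.
- Treat visits up to 6 months as the randomised comparison before crossover.
- Also report baseline-adjusted estimates at 12 and 24 months, which are named NRS timepoints, and label them as following crossover. Adjustment does not remove the effect of crossover on these.
- Keep the t-test as a supportive analysis, stating whether it uses follow-up or change scores.

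The cost is wording and some programming. No patient, visit or measurement is added, and the sample-size calculation stays as it is.
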